#### Secondary analyses

The secondary outcomes will be compared between the three groups at 3 and 6 months using multilevel linear regression adjusting for baseline values and key covariates.

We will consider any difference in attrition rates, and any nonrandomness of the attrition, when comparing outcomes between the three groups. The pattern of missing observations because of loss to follow-up will be examined to determine both the extent of missingness, and whether it is missing at random or is informative. If data are missing to a sufficient extent, the use of appropriate multiple imputation techniques will be considered. Although mortality is possible within the 6-month follow-up period, it is thought to be sufficiently uncommon that methods for joint modelling of survival and longitudinal data will not be necessary.

Further descriptive analyses will explore the relationship between the severity of baseline upper limb function and time since stroke upon the effectiveness of the intervention. There is not sufficient power to perform any formal subgroup analyses. The time pattern of upper limb recovery will be explored by extending the earlier multilevel models to include a further within-patient level (ARAT scores collected at baseline, 3 and 6 months). However, this will depend on the relationship being approximately linear.

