### Case ascertainment and recruitment

Study participants are recruited from both incident and prevalent stroke populations. Participants can be sought from a number of settings in both primary and secondary care including: stroke units; outpatient clinics; day hospitals; community rehabilitation services; and general practices. The study aims to recruit similar numbers of participants within: 0–3 months of stroke; >3–12 months after stroke; and >12 months to 5 years after stroke.

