### Randomisation groups

#### Robot-assisted training using the InMotion robotic gym system

This is delivered using the InMotion robotic gym system which was specifically designed for clinical rehabilitation applications [23–25]. This is currently the most widely used technology for robot-assisted training for patients with moderate to severe upper limb impairment post stroke. The system development started in 1989 and it has amassed the largest body of clinical evidence to date of any robotic system. It has been successfully tested in clinical studies involving over 900 stroke patients and there are around 250 robots in use worldwide.

Participants receive robot-assisted training at the hub sites for up to 45 min per day, three days per week for 12 weeks, in addition to usual care. A detailed description of the robot-assisted training programme using the Template for Intervention Description and Replication (TIDieR) Checklist [26] is provided in Table 1.

**Table 1 Tab1:** Template for Intervention Description and Replication (TIDieR) Checklist for the RATULS trial intervention treatments

Item	Intervention group	
1. Brief name: *‘provide the name or phrase that describes the intervention’*	*Robot-assisted training*	*Enhanced upper limb therapy*

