#### Enhanced upper limb therapy programme

The enhanced upper limb therapy programme aims to match the frequency and duration of the robot-assisted training programme sessions. It has been developed from the upper limb therapy programmes used in the Botulinum Toxin for the Upper Limb after Stroke (BoTULS) trial [27–29] and the Repetitive Arm Functional Tasks after Stroke (RAFTAS) project [30]. Using the principles of person-centred goal-setting and repetitive functional task practice, it aims to drive neuroplasticity and motor recovery after stroke.

Participants receive enhanced upper limb therapy at the hub sites for up to 45 min per day, 3 days per week for 12 weeks, in addition to usual care. A detailed description of the enhanced upper limb therapy programme using the TIDieR Checklist [26] is provided in Table 1.

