### Outcome assessments

Outcomes are assessed at 3 months (±7 days) and 6 months (±7 days) following randomisation.

Assessments are undertaken in two stages:

Stage 1 is a self-completion postal questionnaire consisting of the Stroke Impact Scale (SIS) [33] (3 and 6 months) and the adapted Client Services Receipt Inventory resource utilisation questions (6 months only) [20–22].

Stage 2 is a face-to-face assessment with a researcher blinded to randomisation group. The following data are collected: Barthel ADL Index [16, 17], EQ-5D-5L [18], ARAT [11], Fugl-Meyer Test (motor and sensory arm sections [15]), and adverse events. At the end of the 6-month stage-2 assessment, participants are given a further self-completion questionnaire and are asked to return this by post. This questionnaire contains time and travel resource use questions [34, 35].

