#### Sample size

The sample size is 720 participants (240 participants per group). Responses from 216 participants in each randomisation group will provide 80% power (significance level of 1.67% because of multiple comparisons) to detect a 15% difference in ‘successful outcome’ between each of the three pairs of treatments (robot-assisted training, enhanced upper limb therapy, usual care). We have allowed for 10% attrition and inflated the sample size to 720 participants.

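### The exploratory model of ARAT recovery over time is made to depend on linearity, a condition that three fixed visits do not require

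*Protocol article*

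**What the plan says.** The Objectives section lists, among the exploratory aims, describing the course of upper limb recovery over time within each treatment group. The Secondary analyses section gives the method: "The time pattern of upper limb recovery will be explored by extending the earlier multilevel models to include a further within-patient level", using "ARAT scores collected at baseline, 3 and 6 months". The next sentence sets the condition: "However, this will depend on the relationship being approximately linear". The article gives no criterion for judging this and names no other model if it is not met.

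Three design features bear on the point:

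- **Visits.** The schedule is the same for everyone: "Outcomes are assessed at 3 months (±7 days) and 6 months (±7 days) following randomisation".
- **Treatment period.** Robot-assisted training runs "three days per week for 12 weeks, in addition to usual care", and enhanced upper limb therapy runs "3 days per week for 12 weeks, in addition to usual care".
- **Case mix.** "The study aims to recruit similar numbers of participants within: 0–3 months of stroke", with two further bands covering later times up to 5 years (Case ascertainment and recruitment).

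**The concern.** The sentence is most naturally read as meaning that time enters the model as a straight line; otherwise the condition would have no purpose. Two things follow.

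First, the condition is not needed. Continuous time is useful when participants are measured at many or differing times. Here there are three nominal visits, and a factor with three levels fits any pattern of three means.

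Second, the design makes a departure from linearity plausible. Training stops in two of the three arms at about the middle visit, and about a third of participants are sought within 3 months of stroke. A change of slope at 3 months, possibly differing between arms, is what a reader of this objective would most want to see, and a straight line cannot show it.

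At stake is the usefulness of one exploratory analysis: either its model is not fitted, or it is fitted in a form that hides the feature of interest.

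**Working it through.** The plan states no figure for this analysis, so there is none to reproduce. The check is algebra for a straight line through three equally spaced visits. The visit times come from the protocol; every ARAT value below is assumed for illustration.

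**Timing.** Twelve weeks is 12 × 7 = 84 days, and three months is about 365/4 = 91 days. If training begins soon after randomisation, it ends about a week before the nominal 3-month visit.

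**Slope weights.** For t = 0, 3, 6 the mean is 3 and the deviations are −3, 0, +3, with sum of squares 18. The least-squares slope is Σ(t − 3)y / 18, so the weights on the three values are −3/18 = −1/6, 0 and +3/18 = +1/6. The slope is (6-month value − baseline value)/6, and the 3-month value does not enter it. This holds for complete data with a simple within-person structure such as a random intercept; missing visits would shift the weights somewhat.

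**Patterns the line cannot tell apart.** Gains from baseline in ARAT points:

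| Assumed gain at 0/3/6 months | Slope per month | Fitted values | True gain, first / second half | Line's gain in each half |
|---|---|---|---|---|
| 0 / 3 / 6 | 1.0 | 0 / 3 / 6 | 3 / 3 | 3 |
| 0 / 4 / 6 | 1.0 | 0.33 / 3.33 / 6.33 | 4 / 2 | 3 |
| 0 / 4.8 / 6 | 1.0 | 0.6 / 3.6 / 6.6 | 4.8 / 1.2 | 3 |
| 0 / 6 / 6 | 1.0 | 1 / 4 / 7 | 6 / 0 | 3 |
| 0 / 6 / 4 | 0.67 | 1.33 / 3.33 / 5.33 | 6 / −2 | 2 |

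In the second row the line misses the 3-month mean by only 4 − 3.33 = 0.67 points. A reader could call that close to linear, yet the first-half gain is twice the second-half gain.

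**Level at 3 months.** For assumed means 8, 17, 19 the overall mean is 44/3 = 14.67 and the slope per visit is (19 − 8)/2 = 5.5. The fitted values are 9.2, 14.7 and 20.2, so the line is 17 − 14.7 = 2.3 points low at 3 months.

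**Group difference.** For assumed differences 0, 3, 1 the mean is 4/3 = 1.33 and the slope per visit is 0.5. The fitted differences are 0.8, 1.3 and 1.8. The 3-month difference is understated by (3 − 1.33)/3 = 56%, and a fading effect appears to grow.

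**Simulated illustration.** Two arms of 216 had mean gains 0/3/6 and 0/6/6, with assumed between-person SD 8 and residual SD 5. The linear model gave a group-by-time slope of 0.04 points per month. With visit as a factor, the group differences in change from baseline were 3.9 at 3 months and 0.2 at 6 months. The likelihood-ratio statistic against linearity was 54.6 on 2 df.

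**Parameter count.** Arm-specific lines need 3 intercepts + 3 slopes = 6 mean parameters; visit-by-group needs 3 × 3 = 9. The difference is 3. With a common baseline mean the counts are 1 + 3 = 4 and 1 + 6 = 7, again a difference of 3.

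**The case against.** The strongest reply is that the condition is a safeguard. It tells the analyst not to fit a line to bent data, so the distortions above arise only if it is ignored or applied loosely. Much of this stands. The simulated plateau was flagged decisively by the likelihood-ratio test, so a gross bend should be caught. What remains is the mild bend, as in the 0/4/6 row, which could pass an unspecified judgement of approximate linearity while the slope hides the pattern. Setting such a criterion is ordinary content for an analysis plan that is not shown, so its absence is not counted against the article.

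A reader might infer that the objective would be abandoned if linearity failed. The text does not say so. The condition attaches to the extended multilevel model only, and means by visit and group would still be available from the ARAT scores collected.

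A reader might also infer that the trial's 3-month treatment effect is at risk. It is not. The Primary analysis section compares success at 3 and 6 months by logistic regression, and secondary outcomes are compared at each visit with adjustment for baseline. Neither uses a time trend. These comparisons do not themselves describe the trajectory of the ARAT score, so they do not replace the exploratory model.

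Finally, the documents contain no recovery curves, and about two-thirds of participants are sought more than 3 months after stroke. A bend is plausible; it is not shown to be likely.

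**Conclusion.** The point holds as a minor improvement. The linearity condition is unnecessary with three fixed visits, and it leaves the only named model for a stated exploratory objective either unfitted or unable to separate gains before 3 months from gains after.

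The zero weight of the 3-month value follows from the equal spacing and does not depend on the illustrative numbers. The 2.3-point shortfall, the 56% understatement and the reversed fade do depend on assumed means. They describe what a straight line would do to clearly bent data in this exploratory model and are not estimates for this trial. The documents support no stronger claim about the primary outcome, the sample size or the planned comparisons at 3 and 6 months.

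**What to change.** Delete the sentence that makes the analysis depend on linearity. In its place, state that visit (baseline, 3 months, 6 months) enters the repeated-measures model of ARAT as a categorical factor with visit-by-group terms, that the planned stroke-service level is kept, and that group means and differences at 3 and 6 months will be reported.

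A common baseline mean and an unstructured within-person covariance are reasonable options but are not needed to meet the point. If baseline ARAT stays among the responses, the plan should say how the severity stratum is handled, since that stratum is itself defined from the ARAT score.

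The cost is one sentence and three mean parameters, against 3 × 216 = 648 participants expected to provide responses. No new data are needed. The Trial status section reports recruitment still in progress at 468 patients, so the wording could be settled before final data are seen.

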#### Sample size

The sample size is 720 participants (240 participants per group). Responses from 216 participants in each randomisation group will provide 80% power (significance level of 1.67% because of multiple comparisons) to detect a 15% difference in ‘successful outcome’ between each of the three pairs of treatments (robot-assisted training, enhanced upper limb therapy, usual care). We have allowed for 10% attrition and inflated the sample size to 720 participants.

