The aim of the Robot Assisted Training for the Upper Limb after Stroke (RATULS) trial is to evaluate the clinical and cost-effectiveness of robot-assisted training compared to an upper limb therapy programme of the same frequency and duration, and usual post-stroke care.

The null hypothesis is that there is no difference in upper limb function at 3 months between study participants who receive robot-assisted training and those who receive an enhanced upper limb therapy programme and those who receive usual post-stroke care. The RATULS trial will be making comparisons of the effectiveness of rehabilitation on upper limb function between all three pairs of trial arms.

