### Statistical analysis

#### Primary analysis

The primary outcome is arm function measured by the ARAT [11] at 3 months. It has been suggested that the minimal clinically important difference for the ARAT is 10% of its range (6 points) [37] but a smaller treatment effect may be clinically beneficial in those with severe initial upper limb functional limitation who are likely to improve less than those with more moderate limitation. There will be a stepped approach to define ‘successful outcome’: baseline ARAT 0–7 must improve by 3 or more points; baseline ARAT 8–13 improve by 4 or more points; baseline ARAT 14–19 improve by 5 or more points; baseline ARAT 20–39 improve by 6 or more points. Analyses will be by intention-to-treat. Logistic regression will be used to compare the primary outcome (success) between the three randomisation groups at 3 and 6 months, adjusting for any imbalance in key covariates. The use of multilevel logistic models will be explored. It may be possible to fit three-level models (hubs, spokes and participants), but since there are only four centres with a hub, and a small number of stroke services accessing an InMotion robotic gym system at each hub, it may be necessary to fit a two-level model (stroke services and participants).

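### The equal 1.67% Bonferroni split over three pairwise comparisons is valid but inefficient; a Shaffer step-down gives more power on the second and third pairs within the same 5% limit, at the same sample size

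*Protocol article*

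**What the plan says.** The Background states that the trial will be "making comparisons of the effectiveness of rehabilitation on upper limb function between all three pairs of trial arms". The Sample size section carries this into the design. It states: "Responses from 216 participants in each randomisation group will provide 80% power". The target there is a gap of 15% in the proportion with a successful outcome, for every pair of arms, and the level used is given as a "significance level of 1.67% because of multiple comparisons". On losses to follow-up the section says: "We have allowed for 10% attrition and inflated the sample size to 720 participants".

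The Primary analysis section names logistic regression to "compare the primary outcome (success) between the three randomisation groups at 3 and 6 months". It gives no test level and no order of testing. No step-down, closed or gatekeeping procedure appears anywhere in the article, so the equal split of 5% over three pairs is the only multiplicity rule stated.

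**The concern.** A plain Bonferroni split treats the three null hypotheses as if any combination of them could be true. For three groups that is not so: any two equalities imply the third. Exactly two true nulls is therefore impossible, and guarding against that case costs power.

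The cost falls on questions the trial cares about. The first objective sets robot-assisted training against both enhanced therapy and usual care. The Background asks for evidence free of confounding by therapy dose, which makes robot against enhanced therapy a central comparison. The 80% in the Sample size section is power for one pair at a time; the chance of establishing both robot comparisons is lower.

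**Working it through.** **Inputs from the Sample size section:** 1.67% per pair, 80% power, a difference of 15 percentage points (taken as absolute), 216 evaluable per group, 10% attrition, 240 per group.

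**Assumption:** the article gives no comparator success rate, so several are shown.

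**The plan's own figures**

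- Level: 5%/3 = 1.67%.
- Attrition: 216/0.9 = 240, and 3 × 240 = 720.
- Size per group, pooled two-sided test: n = [z(α/2)·√(2·p̄·(1−p̄)) + z(β)·√(p1(1−p1) + p2(1−p2))]² / (p2−p1)². At 30% v 45%, p̄ = 0.375, z(α/2) = 2.394 and z(β) = 0.842, so n = (2.394 × 0.6847 + 0.842 × 0.6764)² / 0.0225 = 2.208²/0.0225 ≈ 217.
- Power with 216 at 30% v 45%: Φ[(0.15·√216 − 2.394 × 0.6847)/0.6764] = Φ(0.836) ≈ 79.8%.

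The plan's figures are reproduced at a comparator rate of about 30%.

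**Why the step-down keeps the 5% limit**

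- All three nulls true: an error requires the smallest p-value to be at or below 1.67%. Bonferroni bounds that at 5%.
- Exactly one null true: that pair is never tested above 5%, so its error is at most 5%.
- Exactly two nulls true: impossible.
- No Bonferroni rejection is lost: if a pair has p ≤ 1.67%, so does the smallest p-value, and the pair is then rejected first or at 5%.

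The argument also holds for the planned logistic regression, where one pairwise log odds ratio is the difference of the other two.

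**Size of the gain:** simulation with 400,000 replicates per scenario, 216 per group, two-sided pooled z-tests. Each entry is Bonferroni → step-down.

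| Rates in the three arms | Power per true 15-point pair | All true differences found | At least one true difference found | Error on the equal pair |
|---|---|---|---|---|
| 45/30/30% | 79.9% → 86.5% | 68.4% → 81.8% | 91.3%, unchanged | 1.7% → 5.0% |
| 45/45/30% | 79.8% → 86.3% | 68.6% → 81.5% | 91.1%, unchanged | 1.8% → 4.7% |
| 35/20/20% | 87.0% → 92.0% | 78.8% → 88.7% | 95.2%, unchanged | 1.6% → 5.1% |
| 57/57/42% | 77.9% → 84.1% | 65.9% → 78.2% | 90.0%, unchanged | 1.7% → 4.8% |
| 60/45/30% | 77.9% → 87.6% (60 v 45); 79.9% → 90.2% (45 v 30) | 58.8% → 77.8% | 100%, unchanged | none equal |

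With robot at 45% and the other two arms at 30%, the third column is the power for both robot comparisons. At 60/45/30%, the 60 v 45 pair is robot against enhanced therapy. With all three rates equal at 30%, family-wise error is 4.4% under both rules.

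If the middle arm lies halfway (45/37.5/30%), the one 15-point pair gains little (79.9% → 81.2%), while the two 7.5-point pairs go from 22.8% and 20.9% to 36.0% and 33.6%.

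**The case against.** **The 1.67% may be only a planning level.** It stands in the sample-size paragraph, not in the analysis section, and sizing at 5%/3 is compatible with a later step-down test. An analysis plan that is not shown could specify one. That is fair, and it means the article cannot be said to forbid a better rule. It does not remove the point, because the equal split is a rule the article states and the proposal replaces that rule; it does not fill a gap.

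**Bonferroni is valid and gives simple matching intervals.** This stands. The point is about efficiency, not about an error in the plan.

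**The gain is not free.** This also stands. Only the 5% bound is shared. When exactly one pair is equal, the false-positive rate on that pair rises from about 1.7% to about 5%. The simulated maximum of 5.1% reflects the normal approximation.

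Three stronger readings are tempting but not supported:

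- *Success is compared at 3 and 6 months, so six tests share a level meant for three.* The Abstract, the null hypothesis in the Background and the first sentence of Primary analysis all fix 3 months as the primary time point. The later phrase is loose, but it does not make 6 months co-primary.
- *The 80% power is overstated and should read 77–80%.* With 216 per group, power is lowest at 76.8% (42.5% v 57.5%), but it is 82.8% at 25% v 40%, 86.7% at 20% v 35% and 82.8% at 60% v 75%. The lower range alone would be one-sided.
- *720 is the wrong number.* The calculation reproduces at a plausible comparator rate.

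**Conclusion.** The point holds as a cheap improvement in efficiency. Under the stated rule, with 216 per group and rates of 45/30/30%, the chance of establishing both robot comparisons is about 68%; the step-down makes it about 82%. Power per true pair goes from about 80% to 87%. At 60/45/30%, robot against enhanced therapy goes from about 78% to 88%. The gain is on the second and third rejections only, since the first still needs p ≤ 1.67%.

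These sizes rest on assumed success rates, an absolute 15-point difference, exactly 216 evaluable per group and unadjusted z-tests in place of the planned adjusted logistic regression. Power for the true differences rose in every scenario run, and by the argument above the step-down can never reject less than Bonferroni does.

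**What to change.** State in the analysis section that, for 3-month success, the three pairwise p-values are ordered, the smallest is tested at 1.67% and, if it is rejected, the other two are each tested at 5% (Shaffer step-down). If the smallest is not rejected, no pair is. Keep 720 participants and the existing sample-size calculation, which remains valid for the first step.

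The cost is a few lines of text. Confidence intervals that match a step-down test exactly are less simple, so report both 98.33% and 95% intervals for each pair and say which level each test used. If the analysis plan already contains such a rule, a one-line statement in the protocol is enough. Fix the rule before any comparison by arm is seen by those who will analyse the trial. The Trial status section reports 468 recruited at submission, and only the data monitoring committee has unblinded outcome data before the trial ends.
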